## Abstract

**Background:**

The optimal approach to the drainage of malignant obstruction at the liver hilum remains uncertain. We aim to compare percutaneous transhepatic biliary drainage (PTBD) to endoscopic retrograde cholangiography (ERC) as the first intervention in patients with cholestasis due to suspected malignant hilar obstruction (MHO).

**Methods:**

The INTERCPT trial is a multi-center, comparative effectiveness, randomized, superiority trial of PTBD vs. ERC for decompression of suspected MHO. One hundred and eighty-four eligible patients across medical centers in the United States, who provide informed consent, will be randomly assigned in 1:1 fashion via a web-based electronic randomization system to either ERC or PTBD as the initial drainage and, if indicated, diagnostic procedure. All subsequent clinical interventions, including crossover to the alternative procedure, will be dictated by treating physicians per usual clinical care. Enrolled subjects will be assessed for successful biliary drainage (primary outcome measure), adequate tissue diagnosis, adverse events, the need for additional procedures, hospitalizations, and oncological outcomes over a 6-month follow-up period. Subjects, treating clinicians and outcome assessors will not be blinded.

**Discussion:**

The INTERCPT trial is designed to determine whether PTBD or ERC is the better initial approach when managing a patient with suspected MHO, a common clinical dilemma that has never been investigated in a randomized trial.

**Trial registration:**

ClinicalTrials.gov, Identifier: NCT03172832. Registered on 1 June 2017.

**Electronic supplementary material:**

The online version of this article (10.1186/s13063-018-2473-2) contains supplementary material, which is available to authorized users.

## Background

Both percutaneous transhepatic biliary drainage (PTBD) and endoscopic retrograde cholangiography (ERC) are accepted approaches in the management of patients with malignant obstruction at the liver hilum. In routine clinical practice, ERC is generally favored on the basis of: (1) high technical and clinical success rates for other (non-hilar) indications; (2) the perceived safety of ERC relative to PTBD; (3) the perceived ability to perform more comprehensive tissue sampling at the time of ERC compared to PTBD; (4) the avoidance of external tubes which are often needed for PTBD; and (5) because patients with suspected malignant hilar obstruction (MHO) typically present to, and are managed by, gastroenterologists.

However: (1) observational data suggest that PTBD is superior for achieving complete drainage of MHO [1–3] and some guidelines recommend the percutaneous approach over ERC for Bismuth type 3 and 4 hilar strictures [4]; (2) the generally quoted risks of PTBD are based on outdated studies and may be exaggerated [5]; and (3) endoscopic diagnosis of indeterminate biliary strictures remains suboptimal despite the use of cholangioscopy and multi-modal sampling.

Although existing evidence suggests that many patients who undergo initial ERC require subsequent PTBD for adequate drainage [3, 6], no randomized trials comparing the two modalities for suspected MHO have been published. We hypothesize that even though PTBD will be more effective than ERC for decompression of suspected MHO, this advantage will be offset by the favorable safety profile and superior diagnostic capacity of ERC. If, however, PTBD is found to be substantially superior in terms of drainage, or if the potential advantages of ERC are not realized, then the existing clinical approach to MHO must be reappraised. Moreover, identifying patient and stricture characteristics that predict response to PTBD or ERC may be important for informing clinical decision-making and guidelines.

## Methods

### Design

The INTerventional Radiology vs. ERC for Perihilar Tumors (INTERCPT) trial is a multi-center, comparative effectiveness, randomized, superiority trial of PTBD vs. ERC for decompression of suspected MHO. Ethical approval has been obtained from the Institutional Review Board at the primary site (Medical University of South Carolina, Pro00063825) and several sub-sites. The remaining sites will only enroll subjects once local regulatory approval has been obtained.

### Patients

The eligibility criteria are listed in Table 1. Informed consent will be obtained from all study participants. We plan to enroll patients of 40 years of age or older with cholestasis who have radiographic evidence of obstruction at the liver hilum. Thus, patients with a documented hilar stricture on magnetic resonance imaging (MRI) or those with a dilated intrahepatic, but not extrahepatic biliary system, on ultrasound or computed tomography scan (CT) will be eligible. To maximize generalizability, this trial is intended to mimic routine clinical practice as closely as possible, in which the decision to proceed with biliary decompression is often based on information from one – but not all – of these radiographic tests. Patients will be excluded if the hilum is not directly involved, if there is reason to believe that the stricture is benign (because these are typically better managed endoscopically or surgically), or if there are relative contraindications to PTBD or ERC that clearly favor one procedure over the other.

**Table 1 Tab1:** Eligibility criteria

Inclusion criteria
1. Age ≥ 40 years (to reduce the likelihood of enrolling patients with obstruction due to primary sclerosing cholangitis)
2. Cholestatic liver function tests, including serum alkaline phosphatase level ≥ 300 IU/L and bilirubin level ≥ 3.7 mg/dL
3. Radiographic evidence of a biliary hilar stricture *or* intrahepatic *but no extrahepatic* biliary ductal dilation
Exclusion criteria
1. Known radiographic evidence of a Bismuth-Corlette type 1 biliary stricture
2. Known diagnosis of primary sclerosing cholangitis *without* suspicion of dominant hilar stricture
3. Recent cholecystectomy, liver resection, or biliary surgery within 12 months
4. Known Mirizzi syndrome
5. Known IgG4-mediated cholangiopathy
6. Significant liver metastatic disease interfering with safe/effective PTBD
7. Significant ascites interfering with safe/effective PTBD
8. Known regional malignant-appearing adenopathy or extrabiliary mass, indicating the need for concurrent EUS-FNA
9. Prior ERC or PTBD for hilar obstruction
10. Surgically altered luminal anatomy other than prior Billroth reconstruction
11. Standard general contraindications to ERC or PTBD (e.g., hemodynamic instability, uncorrected coagulopathy, etc.)
12. Pregnancy
13. Inability or unwillingness to follow study protocol

*ERC,* endoscopic retrograde cholangiography, *EUS-FNA*, endoscopic ultrasound-guided fine-needle aspiration biopsy, *PTBD* percutaneous transhepatic biliary drainage

### Setting

Patients will be identified and enrolled at approximately 25 tertiary medical centers across the United States, the exact setting in which such patients are managed in routine clinical practice and the decision of PTBD vs. ERC made because their high complexity generally prompts referral to a tertiary center. Non-referral hospitals were not included in the network because MHO patients require not only tertiary and quaternary procedural care (to include interventions like cholangioscopy, intraductal photodynamic therapy, and radiofrequency ablation), but also National Cancer Institute (NCI)-designated cancer center-type expertise in medical and surgical oncology as part of a multi-disciplinary Tumor Board approach.

### Randomization

Eligible patients who provide informed consent will be randomly assigned in 1:1 fashion to PTBD or ERC as the first intervention using a web-based, electronic randomization system. The randomization schedule will be generated centrally at the data coordinating center and will ensure treatment balance within site. The study allocation, interventions, and assessments as adapted from the Standard Protocol Items: Recommendations for Interventional Trials (SPIRIT) Figure, are outlined in Fig. 1; Additional files 1 and 2.

**Fig. 1 Fig1:**
[figure not shown]
Enrollment, intervention, and assessments in the INTERCPT trial

### Procedure

Enrolled subjects will undergo PTBD or ERC according to study group assignment. All components of the procedure and related interventions will be dictated by treating physicians per usual care. Specifically, the technical approach to drainage (e.g., bilateral vs. unilateral, functional lobe only) and tissue sampling (e.g. brushing, intraductal biopsies, cholangioscopy, fluorescence in situ hybridization, etc.) will be determined by the treating physicians and proceduralists performing the PTBD or ERC.

### Blinding

Given the substantial differences in approach between PTBD and ERC, including pre-procedure instructions and consent, post-procedure observation and follow-up, location within a hospital, as well as the need for a percutaneous catheter after PTBD, blinding subjects to study intervention is not possible. Similarly, there is no practical method to ensure masking of treating clinicians and outcome assessors who will be reviewing medical records.

### Follow-up

All follow-up decisions pertaining to the need for repeat procedures to address inadequate drainage or incomplete tissue sampling, or the decision to refer the patient for the alternative procedure will be dictated by treating physicians. All enrolled subjects will be followed for 6 months after the index (randomly assigned) procedure, primarily through review of their medical records.

### Outcomes

The primary endpoint of successful biliary drainage will be defined as a 50% reduction in bilirubin level within 3 weeks of the study intervention without additional ERC or PTBD during that timeframe.

Secondary endpoints will include:An alternative definition of successful biliary drainage, defined as improvement in the serum bilirubin level to ≤ 2.5 mg/dL as a result of the index (randomization) intervention without the need for additional PTBD or ERC. This bilirubin level is considered informative because it is the threshold most commonly used by oncologists to administer chemotherapyAdverse events related to PTBD and ERC, defined according to standard consensus guideline documents published in the interventional radiology [5] and gastroenterology [7] literature, respectivelyMalignant tissue diagnosis, defined as a definitive diagnosis of malignancy documented in the subject’s medical record. We recognize that a fraction of patients will not have malignant obstruction, will not require a tissue diagnosis (known alternative primary cancer), or that a “gold standard” diagnostic test may not be available within the follow-up period in patients who are not diagnosed with cancer. We do, however, expect that patients with cancer in whom a tissue diagnosis is needed and possible will be allocated evenly between study groupsTotal number of procedures, hospitalizations, and cancer-specific treatments during the 6-month follow-up period

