### Statistical considerations

Given patient preference to avoid extracorporeal tubes as well as the other perceived advantages of ERC, we estimate that PTBD would have to be at least 20% more effective in achieving successful biliary drainage to change clinical practice. Assuming that PTBD will be 90% effective in achieving successful biliary decompression, we estimate that 160 patients (80 per study group) would provide a power of at least 85% to detect a 20% absolute difference between study groups on the basis of Fisher’s exact test, with a two-sided significance level of 0.05. To address potential losses to follow-up, the sample size is inflated by 15%. Thus, a total of 184 subjects will be enrolled.

For analysis of the primary endpoint, we will use a chi-square test to compare the proportion of patients achieving a 50% reduction from baseline in serum bilirubin level within 3 weeks in the PTBD and ERC groups using the intention-to-treat (ITT) principle. All randomized subjects will comprise the ITT population. A secondary analysis will explore the potential variability by study site and baseline serum bilirubin on the primary outcome measure. Center differences will be examined by including study site as a covariate in a mixed-effects logistic regression model. Since there will be roughly 25 centers with variable sample sizes, study site will be modeled as a random effect. In addition to the defined ITT analysis sample, a per-protocol sample will be defined as a subset of the ITT sample. This sample will be used for secondary sensitivity analyses of the primary and secondary outcomes. The per-protocol sample will include all randomized subjects that do not have the following protocol deviations: eligibility violation, non-adherence to the randomized treatment, or missing primary outcome. The secondary endpoints will be compared between treatment arms using a chi-square test or *t* test for independent means, as appropriate. There will be no adjustment for multiple comparisons in the pre-specified secondary analyses – including any patient-centered outcomes defined in the planning phase – but all additional exploratory analysis results will be interpreted more conservatively using a significance level of 0.01

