## Discussion

The INTERCPT trial will be the only randomized comparison of PTBD vs. ERC as the initial intervention for patients with suspected malignant hilar obstruction. This is a fundamental question in clinical practice that has remained unanswered because of the practical and methodological complexities of such a trial.

To maximize practicality and generalizability, we have adopted a pragmatic study design that includes only one protocol-driven intervention – randomization to PTBD or ERC. All other clinical decisions are deferred to treating physicians as clinically appropriate. We believe that this experimental question is particularly suited for such a pragmatically designed trial because the varying approaches to managing this highly complex disease process between patients and across practice settings constrains protocol standardization and threatens the generalizability of a more traditional randomized controlled trial (RCT) design. Standardizing procedural approach, re-interventions, and medication administration, for example, would not only be impossible to ensure, but would also critically limit external validity because of the tremendous complexity in decision-making and the extreme variability in approaches between providers and institutions.

We appreciate that physicians may select ERC vs. PTBD based on stricture characteristics and other considerations such as the patient’s overall health and goals of care. However, in many practice settings, ERC is typically attempted first because of its perceived advantages. Moreover, stricture characteristics are often unknown beforehand because routine MRI/ magnetic resonance cholangiopancreatography (MRCP) has not been obtained. Fundamentally, the goal of our study is to determine, at the point of care, whether ERC or PTBD is preferable as the initial treatment of patients with suspected MHO, even though stricture characteristics, resectability status, and a definitive diagnosis may not be known – the exact scenario often faced in real-world clinical practice. Furthermore, this study may determine whether a strategy of routine “planning” MRI/MRCP in these cases to guide procedural selection improves clinical outcomes.

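### The primary endpoint counts only a further ERC or PTBD as failure, so a failed index drainage rescued by another route within 3 weeks is scored as a success

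*Protocol article*

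**What the plan says.** The Outcomes section of the protocol article makes primary success "defined as a 50% reduction in bilirubin level within 3 weeks of the study intervention without additional ERC or PTBD during that timeframe". The list of disqualifying procedures has two entries, ERC and PTBD.

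The first secondary endpoint, based on a bilirubin of 2.5 mg/dL or less, names the same two procedures but also requires that the improvement occur "as a result of the index (randomization) intervention without the need for additional PTBD or ERC".

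Statistical considerations says that the chi-square test will "compare the proportion of patients achieving a 50% reduction from baseline in serum bilirubin level within 3 weeks", by intention to treat. That sentence does not repeat the clause on further procedures.

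Later care is unrestricted. The Abstract states: "All subsequent clinical interventions, including crossover to the alternative procedure, will be dictated by treating physicians per usual clinical care". Follow-up adds that "the decision to refer the patient for the alternative procedure will be dictated by treating physicians", and the Discussion says: "All other clinical decisions are deferred to treating physicians as clinically appropriate". According to Setting, the centres have "expertise in medical and surgical oncology as part of a multi-disciplinary Tumor Board approach".

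**The concern.** The trial asks which procedure, used first, achieves drainage. The clause on further procedures is there so that a bilirubin fall produced by a second intervention is not credited to the first. It covers the two modalities under study and nothing else. If the index procedure fails and the liver is then decompressed by surgery or another route within 3 weeks, a halved bilirubin satisfies the rule as written. A failure of the assigned procedure becomes a success.

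The arms are not equally exposed. Under the design assumptions the ERC arm has three times as many failures as the PTBD arm. The same rescue share in both arms would therefore add more false successes to ERC and narrow the difference that the trial is sized to detect.

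**Working it through.** **1. Does anything else in the document remove such a patient?**
- Outcomes: the patient has a 50% fall within 3 weeks and no further ERC or PTBD, so the definition is met.
- Statistical considerations, primary analysis: it restates only the 50% fall, so the patient is again a success.
- Statistical considerations, per-protocol sample: it excludes eligibility violations, non-adherence to the randomized treatment and missing primary outcomes. A patient who received the assigned procedure and was rescued later has none of these.
- Follow-up, Abstract and Discussion: other interventions are neither prohibited nor assigned a score.

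Nothing removes the patient.

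**2. Reproducing the plan's figures**

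Inputs from Statistical considerations: PTBD success 0.90 ("Assuming that PTBD will be 90% effective in achieving successful biliary decompression"); absolute difference 0.20, hence ERC 0.90 − 0.20 = 0.70; 80 per arm; two-sided 0.05; Fisher's exact test; stated power at least 85%.
- Exact enumeration of Fisher's test: 86.7%, consistent with the stated figure.
- Exact enumeration of the chi-square test, which is the planned analysis: 90.3%.
- Enrolment: 160 × 1.15 = 184, as stated.

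**3. Effect of misscored rescues**

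Let r_E and r_P be the shares of index failures in the ERC and PTBD arms that are rescued by a route other than ERC or PTBD and still reach a 50% fall in time. The document gives neither, so both are assumptions. The calculation also takes 0.90 and 0.70 as the true success rates of the index procedure alone.
- Scored ERC success = 0.70 + 0.30 r_E
- Scored PTBD success = 0.90 + 0.10 r_P
- Scored difference = 0.20 + 0.10 r_P − 0.30 r_E

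With the same share r in both arms, the difference is 0.20 × (1 − r):

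| r, both arms | PTBD | ERC | Difference | Fisher power | Chi-square power |
|---|---|---|---|---|---|
| 0 | 0.900 | 0.700 | 20.0 points | 86.7% | 90.3% |
| 5% | 0.905 | 0.715 | 19.0 points | 84.1% | 88.3% |

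In patients, the ERC arm would have 80 × 0.30 = 24 failures and the PTBD arm 80 × 0.10 = 8. At r = 5%, 24 × 0.05 = 1.2 ERC patients and 8 × 0.05 = 0.4 PTBD patients are misscored.

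**4. Direction when the shares differ**

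The difference narrows if r_P < 3 r_E and widens if r_P > 3 r_E. For example, 5% in the ERC arm only gives 0.20 − 0.015 = 18.5 points; 5% in the PTBD arm only gives 0.20 + 0.005 = 20.5 points. The direction cannot be fixed from the document.

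**The case against.** **The expected rescues are already covered.** After inadequate drainage the article describes a repeat procedure or the alternative procedure, and both disqualify. It never mentions surgical bypass or endosonography-guided drainage; endosonography appears only for needle aspiration, in an exclusion criterion. A misscored case needs four things together: the index procedure fails, no ERC or PTBD follows within 3 weeks, another route is used, and bilirubin still halves by day 21. This stands, and it limits the size of the problem. It does not change how such a patient is scored.

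**The article is condensed.** Rare intervening procedures may be dealt with in a fuller document. That would excuse silence, but here the article states the operative rule and lists what disqualifies. The list itself is too narrow.

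**The secondary endpoint might seem to supply the remedy.** A reader might infer that its attribution wording was dropped from the primary endpoint by mistake and should be restored. The document does not support this. The secondary definition states no time window, whereas the primary is tied to 3 weeks from the study intervention, and both name the same two procedures. Under Blinding, outcome assessors are unmasked and work from medical records. An attribution clause would bring a causal judgement, made with knowledge of the arm, into an endpoint that otherwise needs only bilirubin values and a record of procedures.

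**Conclusion.** The gap is real on the stated wording: rescue by a route other than ERC or PTBD is scored as success of the assigned procedure. The effect is probably small. At an assumed 5% of failures in both arms, the difference loses 1 point and power falls by 2 to 3 percentage points. That takes the Fisher figure just below the stated 85% but leaves the planned chi-square test above it. These figures are an illustration resting on an assumed share and on the design rates being true index-procedure rates. None of the plan's stated figures is shown to be wrong.

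A reader might infer a serious loss of power by supposing that 10% to 30% of failures are rescued this way, or that it happens only after ERC. Nothing in the document supports those shares or that asymmetry. Nor does it follow that the endpoint no longer answers the trial's question; a small number of patients could be misscored. The case for changing the wording is that the rule does not match its purpose and is almost free to correct.

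**What to change.** In the primary endpoint, replace the clause on further ERC or PTBD with: *without any additional biliary drainage procedure by any route (including ERC, PTBD or surgical drainage) during that timeframe*. Use the same list of procedures in the secondary drainage endpoint, and carry the clause into the primary analysis sentence in Statistical considerations so that the two sections define the same outcome.

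Do not add the attribution wording to the primary endpoint; the broader list closes the gap and keeps the rule objective. How to score an early resection is a choice about what the trial is estimating, not a correction, and is left to the sponsor to state.

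The change affects scoring only and restricts no treatment, so the pragmatic design is unaffected. It costs one field in the chart review, in a trial that already counts total procedures over 6 months, and a few more patients will be scored as non-successes.

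### Adverse events are defined by one consensus document for PTBD and another for ERC, then compared between arms, so part of any safety difference may come from the definitions.

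*Protocol article*

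**What the plan says.** In the protocol article, the Outcomes section lists adverse events related to PTBD and ERC as a secondary endpoint, "defined according to standard consensus guideline documents published in the interventional radiology" and gastroenterology literature. The sentence closes with the word *respectively*, which ties the radiology source to PTBD events and the gastroenterology source to ERC events.

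Statistical considerations then states: "The secondary endpoints will be compared between treatment arms using a chi-square test or" a t test, as appropriate. It makes no exception for adverse events.

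Three other sections bear on the point:

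- **Randomization:** patients are "randomly assigned in 1:1 fashion to PTBD or ERC as the first intervention".
- **Follow-up:** "the decision to refer the patient for the alternative procedure will be dictated by treating physicians", so a patient may have both procedures.
- **Blinding:** "there is no practical method to ensure masking of treating clinicians and outcome assessors who will be reviewing medical records".

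The Background hypothesis is that PTBD will drain better but that "this advantage will be offset by the favorable safety profile and superior diagnostic capacity of ERC".

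**The concern.** A between-arm comparison needs the same measuring rule in both arms. Here the rule follows the procedure, and the first procedure is the randomised treatment. If the two documents differ in what they count as an event, two arms with identical complications can show different rates. A real difference can equally be hidden. Randomisation balances patients, not definitions, and a larger sample only makes the artefact more precise.

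This matters more than for a routine secondary endpoint. The Background presents the trial as a trade-off between better drainage with PTBD and better safety and diagnosis with ERC, and says current practice must be reappraised if ERC's advantages do not appear. The adverse event comparison is the most direct evidence on the safety side.

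**Working it through.** **1. The plan's own figure.** The article gives no figure for the adverse event comparison. Its only power statement concerns the primary endpoint: "160 patients (80 per study group) would provide a power of at least 85% to detect a 20% absolute difference between study groups". Full enumeration of Fisher's exact test with 80 per group, 90% against 70% and two-sided 0.05 gives a power of 0.867, so the statement reproduces. Nothing below changes it.

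**2. How definition and arm are linked.** The Outcomes section attaches a definition to each procedure. Randomization fixes the first procedure by arm. Hence events of the index procedure are judged by the radiology source in the PTBD arm and by the gastroenterology source in the ERC arm. Only events of a later, alternative procedure are judged by the other source.

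**3. Size without crossover.** Inputs:

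- n = 92 per arm, from 184 / 2 (Statistical considerations and 1:1 allocation).
- R, the true proportion of patients with an event, equal in both arms. Assumed 15%, 25% or 35%.
- c, the fraction of those events that the narrower definition counts, the wider one counting all. Assumed 1.0 down to 0.5.

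The counted proportions are R and cR, so the spurious difference is R(1 − c). The false-rejection rate is the sum, over all pairs (x, y), of Bin(x; 92, R) × Bin(y; 92, cR) for which the uncorrected chi-square test has p ≤ 0.05. The test statistic is z = [(x − y)/n] / √[p̄(1 − p̄)·2/n], with p̄ = (x + y)/(2n).

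Each cell gives the spurious difference in percentage points, then the false-rejection rate:

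| c | R = 15% | R = 25% | R = 35% |
|---|---|---|---|
| 1.0 | 0; 4.9% | 0; 5.1% | 0; 5.2% |
| 0.9 | 1.5; 5.9% | 2.5; 6.8% | 3.5; 8.1% |
| 0.8 | 3.0; 9.0% | 5.0; 12.7% | 7.0; 17.7% |
| 0.7 | 4.5; 14.9% | 7.5; 23.6% | 10.5; 34.7% |
| 0.6 | 6.0; 24.0% | 10.0; 39.6% | 14.0; 56.9% |
| 0.5 | 7.5; 36.8% | 12.5; 59.0% | 17.5; 78.1% |

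The first row is the situation under one common definition: the test keeps its nominal 5%. With 80 per arm, the rates for c from 0.9 to 0.5 run from 5.6% to 72.5%.

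**4. Effect of crossover.** Let f₁ and f₂ be the shares of events in the two arms that are judged by the other arm's document. The counted proportions become R[(1 − f₁) + c·f₁] and R[c(1 − f₂) + f₂]. Their difference is R(1 − c)(1 − f₁ − f₂). Crossover therefore shrinks the artefact in proportion to f₁ + f₂ and cancels it only if the two shares add to 1. The article gives no crossover rate, so the table shows the undiluted case.

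**5. Direction.** If the radiology source is the narrower one, PTBD looks safer than it is. If the gastroenterology source is, ERC does. The article does not show which applies.

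**The case against.** The strongest reply is that the harm depends on two documents that are not shown. If they largely agree, little happens: at c = 0.9 the false-rejection rate is only 6% to 8%. This stands. The article supports saying that the comparison can be distorted, not that it is, by how much, or in which direction.

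Other parts of the reply also stand:

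- Definitions attach to the procedure, not strictly to the arm, so crossover brings both documents into both arms and dilutes the effect.
- Some risks belong to one procedure only, so each specialty's own definitions are a reasonable basis for descriptive reporting.
- No severity-graded endpoint is stated. A reader might infer that the same event will be graded severe in one arm and not in the other, but nothing in the article shows this.
- Unmasked assessment is disclosed and explained, and would remain under a common definition. It is context, not part of this defect.
- Nothing in the article excludes events after a later procedure. Counting them under the common rule makes this explicit and is not a correction of a stated error.

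One part does not stand: that this is a detail left to the full protocol or the analysis plan. The article does not merely omit a common definition. It states procedure-specific ones and a between-arm test, and a later document would have to override that.

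**Conclusion.** The concern holds in limited form. The article fixes two definition sources by procedure and then compares arms that differ by procedure. An adverse event difference may therefore partly reflect the definitions, and crossover does not in general remove this.

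Under the assumed values, and before any dilution by crossover, the artefact is about 1.5 to 17.5 percentage points, with false rejection of about 6% to 78%. Both figures depend on the true event rate as well as on the divergence of the definitions. Neither R nor c comes from the article.

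A reader might go further and infer that the trial can say nothing about the safety part of its hypothesis. The article does not support that. It also compares the total number of procedures and hospitalizations over 6 months, which depend on neither definition document and capture part of the burden of complications. The hypothesis rests on diagnostic capacity as well.

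Severity is moderate: this is one of several secondary endpoints, and the primary endpoint, its test and the sample size are unaffected.

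**What to change.** For the between-arm safety comparison, apply to every patient in both arms:

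- one procedure-neutral list of adverse events, for example the union of the events in the two consensus documents;
- one severity scale;
- one time window starting at randomisation, counting events after any subsequent biliary procedure, whichever kind it is.

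Fix this rule in writing before any arm-level adverse event data are examined. Keep the two specialty classifications as descriptive tables by procedure, without a between-arm test.

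The cost is modest: a change to the adverse event form and the analysis plan, and some recoding of events already recorded. Enrollment began in October 2017, but follow-up is mainly by review of medical records, so recoding should be feasible. The price is that the compared rates will be less directly comparable with each specialty's literature, which the descriptive tables largely make good.
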